**Methods/design:**

The trial is a multicenter, randomized, parallel-group, non-inferiority study. Three hundred and twelve patients will be randomly assigned to a Ma’s bamboo-based medicinal moxibustion group (*n*=156) and an acupuncture group (*n*=156). Patients in each group will receive treatment every day, 6 times a week, 12 times in total. Follow-up will be conducted 14 days after treatment. The primary outcome will be the visual analog scale(VAS) at baseline, after 6 times of treatment, end of treatment, and follow-up. The secondary outcomes will include Oswestry disability indexes (ODI), modified Japanese Orthopaedic Association low back pain (M-JOA) score, serum β-endorphin (β-EP), and serum substance P (SP). β-EP and SP, as well as safety evaluation indexes (routine blood, liver, and kidney function and electrocardiogram), will be measure at baseline and after the end of treatment. The number, nature, and severity of adverse events will be recorded.

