### Sample size calculation

The PASS software version 15.0 (NCSS, LLC. Kaysville, UT, USA.) was used to estimate the sample size. The trial is designed to determine the efficacy of Ma’s bamboo-based medicinal moxibustion therapy on low back pain in LDH and prove that its clinical efficacy is not inferior to normal acupuncture therapy. Therefore, we chose a non-inferiority trial design. According to the previous literature [8, 18] and the joint consideration of clinicians and statisticians, it is assumed that the standard deviation of VAS score reduction of patients using bamboo-based medicinal moxibustion is 2.0, the non-inferiority margin was set at 0.78, the significance level of the test is unilateral 0.05 and power of the test is 90%. According to the 1:1 grouping, the sample size required by each group was 140 cases, and the lost follow-up rate will be estimated at 10%. The final sample size of the treatment group and the control group was 156 cases respectively, and the total sample size was 312 cases.

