### Randomization, allocation, and implementation procedures

Central randomization will be conducted by INTELLIGENCE FUTURE Soft Co., Ltd. (Tianjin, China). A random sequence will be generated with SAS 9.2 (SAS Institute, Inc., Cary, NC, USA) by an independent statistician who is not involved in the study, and the sequence will be stored in a central randomization system (interactive web response (IWR) system). Allocation will adopt a stratified random method. Stratified block randomization will be carried out by third party statisticians who will be not involved in any other part of the trial. The patients will be stratified based on the two different centers and randomly assigned to the Ma’s bamboo-based medicinal moxibustion group and the acupuncture group in a 1:1 ratio. The Ma’s bamboo-based medicinal moxibustion group will receive Ma’s bamboo-based medicinal moxibustion therapy. Regular acupuncture therapy will be performed on the acupuncture group. There are two investigators at each center (referred to as A and B). Investigator A will log in to the central randomization system on the computer and be responsible for inputting baseline data of patients, waiting for the system to assign random numbers and grouping, but he will not know the details of grouping and will not participate in treatment. Investigator B is responsible for performing treatment according to the grouping. Due to the nature of the intervention, it is not feasible to conceal the assignment from Investigator B and the patient, but Investigator B will not be permitted to disclose any information about his treatment to Investigator A or the patient. At each visit, A is responsible for collecting data and entering the data in the electronic data capture (EDC) system. The therapist and the data collector are separate. Statisticians are responsible for data processing and are not aware of the grouping until the end of the trial.

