### Statistical analysis

Data analysis will be conducted in accordance with the intention-to-treat principle. Missing data will be handled using linear mixed effects models. Statisticians and chief investigators will work out an analysis plan and related forms before the database lock. The analysis will include case distribution, comparison of basic values, compliance, effectiveness, factors that influence efficacy, and safety. Subgroup analysis will be performed according to pathological classification and syndrome classification. Statistical analysis will be conducted using SAS 9.2 (SAS Institute Inc., Cary, NC, USA). The Wilcoxon rank-sum test, *t* test, or variance analysis will be performed for inter-group or intra-group comparison according to data distribution. The Wilcoxon rank-sum test will be used to compare ranked data. The chi-square test will be applied to compare enumeration data. All tests will be one-sided. A *p* value <0.05 will be considered statistically significant.

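### A rank-sum test is listed for same-patient comparisons, and the article does not say whether the mixed model or a distribution-chosen test decides non-inferiority

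*Protocol article*

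**What the plan says.** All of the following is in the protocol article.

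- **Tests (Statistical analysis).** One list (Wilcoxon rank-sum, t test, variance analysis) serves both kinds of comparison. The tests "will be performed for inter-group or intra-group comparison according to data distribution". The rank-sum test is named again for ranked data. No signed-rank test is named.
- **Missing data (same section).** The analysis follows intention to treat, and "Missing data will be handled using linear mixed effects models". The mixed model has no other stated use.
- **Later plan (same section).** "Statisticians and chief investigators will work out an analysis plan and related forms before the database lock".
- **Stratification (Randomization, allocation, and implementation procedures).** "The patients will be stratified based on the two different centers".
- **Repeated measurement (abstract, Methods/design).** VAS is taken "at baseline, after 6 times of treatment, end of treatment, and follow-up". Serum β-EP and SP are taken at baseline and after treatment.
- **Margin (Sample size calculation).** The quantity is the reduction in VAS, with SD 2.0, margin 0.78, one-sided alpha 0.05, 90% power and 10% loss to follow-up.

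**The concern.** There are two separate problems.

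First, an intra-group comparison here sets later values against baseline values in the same patients. The rank-sum test treats the two sets as unrelated samples. This is a test stated wrongly, which is different from a detail left for later.

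Second, the article gives two routes to the primary result and does not choose between them. A mixed model uses incomplete records inside its own likelihood. It does not produce a completed data set for a t or rank-sum test, which by itself uses only patients with a value at the visit tested. The routes can therefore rest on different patients. They can also answer different questions, because non-inferiority is framed as a mean difference against 0.78, and a rank-sum p-value estimates no mean difference. Choosing the test by data distribution leaves the deciding analysis open until the data are in hand. At stake are one clear answer to the non-inferiority question, some precision, and correct p-values for within-group change.

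**Working it through.** **1. The plan's own figure.** Formula: n per group = 2 × SD² × (z_alpha + z_power)² / margin².
- One-sided 0.05: 2 × 4 × (1.645 + 1.282)² / 0.78² = 112.6, so 113 (114 with the t distribution).
- One-sided 0.025: 2 × 4 × (1.960 + 1.282)² / 0.78² = 138.2, so 139 (140 with the t distribution).
- Loss: 140 / 0.9 = 155.6, so 156, as stated.

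The stated 140 thus matches one-sided 0.025, although the text says 0.05. That is a separate matter. It bears on this point only through the level of the confidence limit in the fix. The formula is for a difference in mean change, so the margin is a mean-difference margin.

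**2. Missing data.** The design expects 156 − 140 = 16 patients per group without follow-up, 32 in all. A test at a single visit, with nothing filled in, leaves them out; a mixed model keeps any earlier post-baseline values they have. The article gives nothing from which to size the effect on the estimate.

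**3. Gain from baseline adjustment.** Assumptions not in the article: baseline SD s0 = 0.87 (uniform over the eligible range 3 to 6, 3/√12) or 1.0, and correlation r between baseline and follow-up. The follow-up SD s1 is set so that the change SD is 2.0:

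s1 = r·s0 + √(4 − s0²(1 − r²)); variance ratio (adjusted / change score) = s1²(1 − r²) / 4.

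| r | ratio, s0 = 0.87 | ratio, s0 = 1.0 |
|---|---|---|
| 0 | 0.81 | 0.75 |
| 0.2 | 0.94 | 0.91 |
| 0.3 | 0.99 | 0.96 |
| 0.4 | 1.00 | 1.00 |
| 0.5 | 0.98 | 0.99 |

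The ratio reaches exactly 1 at r about 0.40 (s0 = 0.87) or 0.45 (s0 = 1.0). The gain is 0% to 25%, and 0% to 4% for r from 0.3 to 0.5.

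**4. Unpaired test on paired data.** Under the same assumptions, with n patients, the unpaired SE is √((s0² + s1²)/n) and the paired SE is 2.0/√n. The ratio is √(s0² + s1²) / 2.

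| r | s0 = 0.87 | s0 = 1.0 |
|---|---|---|
| 0.3 | 1.13 | 1.14 |
| 0.5 | 1.22 | 1.26 |
| 0.7 | 1.33 | 1.38 |

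This is the large-sample result for means, used as a guide for the rank-sum test. At nominal one-sided 0.05 the true size is 1 − Φ(1.645 × ratio): about 0.032 at 1.13 and 0.012 at 1.38.

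**5. Leaving out centre.** If centre explains a share v of outcome variance (assumed), the true size of an unstratified one-sided 0.05 test is 1 − Φ(1.645 / √(1 − v)): 0.049, 0.046 and 0.041 for v = 1%, 5% and 10%.

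The errors in steps 4 and 5 are in the conservative direction.

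**The case against.** The strongest reply is that this is a condensed article and an analysis plan is promised before database lock. Centre terms, baseline covariates and covariance structures are commonly left to such a plan. That stands: their absence from the article is not a defect in itself. It does not excuse the rank-sum test for intra-group comparison, which is stated, or two analyses named side by side with no order between them.

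A reader might infer more than the text supports:

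- **That baseline VAS is ignored.** The sample size rests on VAS reduction, so a change-score analysis is implied and each patient's baseline is used. Only covariate adjustment is unnamed.
- **That every listed test is unpaired and blind to centre.** A t test may be paired, and variance analysis may carry a centre term or repeated measures. Pairing is clearly lost only for the rank-sum test.
- **That the mixed model and the tests contradict each other, or breach intention to treat.** The article does not say that the tests run on complete cases, and they may be meant for baseline or secondary variables. The text supports only that the two are not reconciled.
- **That false-positive risk rises.** Ignoring centre or positive pairing lowers it. Within-group p-values do not decide non-inferiority in any case.
- **That the unpaired SE is up to 1.8 times too large.** That figure comes from 1/√(1 − r) at r = 0.7 with equal SDs at both times. Equal SDs of 0.87 to 1.0 at r from 0.3 to 0.7 imply a change SD of only 0.67 to 1.18, against the article's 2.0.

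A rank-sum test could be run after shifting one group by 0.78. It would then test a location shift, which equals the mean difference only if the two distributions have the same shape. The article mentions neither the shift nor that assumption.

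**Conclusion.** The point holds in a limited form. The rank-sum test is wrong for same-patient comparisons as written. The analysis that decides non-inferiority is not fixed between the mixed model and a test chosen by distribution, and one of those tests, the rank-sum, does not address the 0.78 margin.

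The cost is modest. Leaving out centre or pairing makes the tests conservative. The variance gain from baseline adjustment is 0% to about 25% for assumed correlations of 0 to 0.5. The within-group SE excess is a factor of about 1.13 to 1.38 for assumed correlations of 0.3 to 0.7. Both ranges rest on a change SD of 2.0 and an assumed baseline SD of 0.87 to 1.0. The effect of leaving out patients with missing visits cannot be sized from the article. The main reason to act is that one primary analysis should be settled in advance, and settling it costs little.

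**What to change.** 1. **Primary analysis.** Make the linear mixed model already named the single primary analysis of VAS change, with treatment, visit, treatment-by-visit, baseline VAS and centre.
2. **Non-inferiority decision.** Name one visit before database lock. Compare the confidence limit for the adjusted mean difference at that visit with 0.78, at a level that matches the stated one-sided alpha. For 0.05 this is a limit of the two-sided 90% interval; a 95% interval would silently change the stated error rate to 0.025.
3. **Secondary outcomes.** Adjust ODI, M-JOA, β-EP and SP for baseline and centre in the same way.
4. **Within-group description.** Replace the rank-sum test by a paired t or signed-rank test. Keep rank-sum for independent groups, outside the primary decision.

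The Protocol amendments section says that analyses stay fixed after first enrolment and then allows approved changes. Enrolment has begun, so record this as a documented amendment as well as in the analysis plan. The cost is wording, that approval step and slightly more programming; no new data are needed.

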### Study objectives

The objective of this randomized controlled trial is to evaluate the efficacy and safety of Ma’s bamboo-based medicinal moxibustion therapy in the treatment of patients with LDH low back pain. The specific objectives are (1) to evaluate the effectiveness of Ma’s bamboo-based medicinal moxibustion therapy in improving pain, lumbar dysfunction, daily living ability, and regulating of serum β-endorphin (β-EP) and serum substance P (SP) content in patients with LDH low back pain and (2) to evaluate the safety of this therapy by recording blood routine, liver and kidney function, electrocardiogram results, and the number, nature, and severity of adverse events.

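### The blanket rule that every test is one-sided at 0.05, with no direction stated, is justified only for the VAS non-inferiority comparison and should be two-sided elsewhere

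*Protocol article*

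**What the plan says.** The Statistical analysis section of the protocol article lists the analyses to be done: baseline values, compliance, efficacy, factors influencing efficacy, and safety. It adds subgroup analyses by pathological type and by syndrome type. It names the Wilcoxon rank-sum test, the t test and analysis of variance, and for counts: "The chi-square test will be applied to compare enumeration data". It then closes with "All tests will be one-sided" and a p "value <0.05 will be considered statistically significant". No comparison is exempted and no direction is given for any of them.

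The Sample size calculation section covers only the primary comparison: "the significance level of the test is unilateral 0.05 and power of the test is 90" per cent, and "the non-inferiority margin was set at 0.78". No margin or directional hypothesis is given for any other outcome. Safety is one of the two specific objectives ("to evaluate the safety of this therapy by recording blood routine, liver and kidney function", with ECG and adverse events).

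**The concern.** A one-sided test is natural for non-inferiority, because the margin fixes which side matters. None of the other comparisons has that structure.

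- **Secondary outcomes.** ODI, M-JOA, beta-endorphin and substance P have no margin. A one-sided 0.05 test of no difference accepts, in the tested direction, any result with a two-sided p between 0.05 and 0.10.
- **Unstated direction.** The article says which end of the ODI and M-JOA scales is worse. For the two serum markers it says only that their levels may be related to pain reduction. A direction not fixed in advance can be chosen once the data are known, and a nominal one-sided 0.05 test then behaves like a two-sided 0.10 test.
- **Fit to the named tests.** The ANOVA F test and a chi-square test with more than two categories have no direction, so the rule cannot be applied to them. Baseline comparisons have no favourable side.
- **Safety.** The Safety monitoring section expects different events in the two arms: skin and burn-type events with moxibustion, fainting and needle-related bleeding with acupuncture. Differences could go either way, and a directional test sees only one of them.

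**Working it through.** **1. Directional error per test.** A one-sided test at 0.05 uses z = 1.645 and puts 5% in the tested direction. A two-sided test at 0.05 uses z = 1.960 and puts 2.5% in each direction. The ratio is 5 / 2.5 = 2.

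**2. Four secondary outcomes** (ODI, M-JOA, beta-endorphin, substance P), one test each, independence assumed. Chance of at least one false positive in the tested direction:
- one-sided 0.05: 1 − 0.95^4 = 18.5%
- two-sided 0.05: 1 − 0.975^4 = 9.6%

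**3. Safety tests that are run directionally.** The article gives no event rates, so these are assumptions. With n = 156 per arm and rates p1 < p2, let d = p2 − p1, let SE0 be the pooled standard error and SE1 the unpooled one. Power toward the excess is Φ[(d − z·SE0)/SE1]. Power when the test points the other way is Φ[(−d − 1.645·SE0)/SE1].

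For 2% against 8%: SE0 = √(2 × 0.05 × 0.95 / 156) = 0.0247 and SE1 = √((0.0196 + 0.0736)/156) = 0.0244.

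| Assumed rates | Two-sided 0.05 | One-sided, toward the excess | One-sided, away from it |
|---|---|---|---|
| 2% vs 8% | 68% | 79% | about 0.002% |
| 5% vs 12% | 60% | 72% | about 0.005% |

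A one-sided safety test therefore gains power if it points toward the harm and has practically none if it points away.

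**4. Sample size, to see what a change to the primary test would cost.** Inputs from the Sample size calculation section: "the standard deviation of VAS score reduction of patients using bamboo-based medicinal moxibustion is 2.0", margin 0.78, power 90%, one-sided 0.05, and "According to the 1:1 grouping, the sample size required by each group was 140 cases"; 10% loss to follow-up; 156 per group in the end. A true difference of zero is assumed.

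Normal formula: n = 2·SD²·(z_alpha + z_beta)² / margin², with 2 × 4 / 0.6084 = 13.149.
- As stated, one-sided 0.05: 13.149 × (1.645 + 1.282)² = 112.6, so 113 per group. The exact t calculation gives 114. After dropout (n / 0.9) this is 126 or 127. The stated 140 is not reproduced.
- One-sided 0.025: 13.149 × (1.960 + 1.282)² = 138.2, so 139 per group. The exact t calculation gives 140, and 140 / 0.9 = 155.6, so 156. Both stated figures are reproduced.

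With 140 per group, power by the t calculation is 94.6% at one-sided 0.05 and 90.2% at one-sided 0.025.

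**The case against.** Several things can be said for the plan, and part of it stands.

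- **Total error is not doubled.** If the direction is fixed beforehand, each test has a 5% type I error under either rule. Only error in the chosen direction doubles. After the change, four independent two-sided tests still carry an 18.5% chance of some false positive in one direction or the other. This stands: the rule is faulty for its direction and its reach, and changing it does not deal with multiplicity.
- **Safety.** A reader might infer that safety tests here cannot detect harm and that a null safety result would be uninformative. The article does not support that. It states no direction. A chi-square test on event counts in its usual form flags differences both ways, and safety also rests on recording and following up events. The loss arises only where a test is actually run directionally, and on the side it ignores.
- **Subgroups.** One might treat the three pathological and four syndrome types as seven independent tests and quote 30% against 16% (1 − 0.95^7 and 1 − 0.975^7). This should not be used. The two classifications divide the same patients, and the article does not say that each level is tested separately.
- **Secondary claims.** The article states no superiority hypothesis for any secondary outcome, so it does not follow that superiority will be claimed.
- **Independence.** ODI and M-JOA overlap in content and come from the same patients, so 18.5% and 9.6% are illustrative.
- **A later analysis plan.** One is promised before database lock. But the sidedness rule is not left to it: the article states the rule outright, and its Protocol amendments section says analyses will not be modified after first enrolment.

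**Conclusion.** The point holds. The article fixes a rule that is right in form for one comparison and unjustified for the rest. The firm figure is the per-test doubling of directional error, 5% against 2.5%, which needs no assumption beyond the stated threshold. The 18.5% against 9.6% for four outcomes assumes independence. The open direction and the misfit with the F test and multi-category chi-square tests follow from the text alone. The safety consequence is conditional on a directional test, and its power figures rest on assumed event rates.

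The primary non-inferiority test is not invalidated by this sentence, so the consequences fall on supporting and safety analyses. The change should be made, but the trial's main conclusion does not turn on it.

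**What to change.** In the Statistical analysis section, replace the blanket sentence with wording such as: *One-sided testing is restricted to the primary VAS non-inferiority comparison. All other comparisons are two-sided at 0.05 with 95% confidence intervals. Adverse events are reported by arm, with two-sided 95% confidence intervals for differences.*

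The level of the primary test is a separate decision. If it is set to one-sided 0.025, the Sample size calculation section must be changed from 0.05 in the same amendment, or the two sections will contradict each other. That change keeps 140 per group, 156 after 10% dropout and 312 in total. If the primary test stays at one-sided 0.05, the stated 140 still needs explaining, since the stated inputs give 113 to 114.

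The cost is slightly fewer nominally significant secondary results, and an amendment with ethics committee approval by the route in the Protocol amendments section, because enrolment began in November 2020. No extra patients are needed.

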### Safety monitoring

Possible adverse events during Ma’s bamboo-based medicinal moxibustion treatment include itching, scald, redness, blister, and infection. Fainting, sticking of needle, hematoma, subcutaneous hematoma, and bleeding might occur during acupuncture treatment. Therapists and subjects are informed to actively report any adverse events during the study. Researchers will track the results of safety evaluation indexes (routine blood test, liver and kidney function, ECG) before and after treatment in a timely manner, and confirm the occurrence of adverse events. Any adverse events that occur during the trial will be recorded in a CRF by researchers and patients will be treated as soon as possible. Patients may choose to withdraw from the trial due to any adverse events. The sponsor and the data management company INTELLIGENCE FUTURE will monitor the implementation of the trial protocol and filling of CRFs.

### Protocol amendments

The eligibility criteria, results, and analyses will not be modified once the first participant has been enrolled in the study. Any significant modifications to the protocol, such as study objectives, study design, eligibility criteria, sample size, results or analysis changes, will be approved by the Research Ethics Committee and the person in charge of the project leader and submitted to the relevant ethical review body.

